**Fig 5 pone.0293921.g005:**
[figure not shown]
Markov chain model. From the Core affect model of Russel we can compute 12 complete transitions between affective states, we can insert them in a randomized sequence, calculate transition between blocks and state trait indexes, and once the variability indexes have been relativized, we can fit them into a Markov matrix.

By doing so, we effectively capture the probability of transitioning between and into blocks, empowering to uncover the intricacies of affect dynamics in both music’s auditory realm and images’ visual domain.

From each subject’s data and for each physiological signal, we extracted and analyzed only the main-diagonal indexes, denoted as state trait indexes (AA-BB-CC-DD), which convey the subject’s probability of remaining anchored in a specific affective state (stability).

This meticulous methodology allows us to rigorously assess and understand the dynamics of affective experiences through the lens of Markov chains, offering valuable insights into the temporal evolution of emotional states in our experimental context.

Our anticipated outcomes encompass the following hypotheses:

For participants within the control group, we hypothesize that there will be no statistically significant differences between the scores obtained at T0 and T1, both for measures of cognitive flexibility and affective flexibility. This expectation suggests that individuals in the control group are likely to maintain stable levels of cognitive and affective flexibility over time.Conversely, we expect an interaction effect between group membership (patients) and time (T0 to T1). This interaction effect signifies our hypothesis that cognitive flexibility measures will exhibit improvement over time among patients, leading to concurrent enhancements in affective flexibility. In particular, motor rehabilitation could have a significant impact on executive function, related to mental flexibility, while cognitive-behavioral therapy of individuals with AN could have an impact on both executive function and emotional flexibility.

In essence, our statistical analysis anticipates that patients will demonstrate increased cognitive and affective flexibility throughout the study period.

These hypotheses provide a clear framework for our statistical analysis and offer valuable insights into the expected outcomes of this multifaceted assessment of flexibility.

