**Fig 3 pone.0293921.g003:**
[figure not shown]
IAPS protocol. The IAPS protocol first involves careful selection of images consistent with the affective states quadrant (top part of the figure) and then implementation into a sequence consisting of 13 image blocks, resulting in 12 possible transitions for analysis. Emotional elicitation is then measured in physiological terms by f-EMG, GSR, ECG, RSP. The stimuli images shown are for illustration purposes only and are not the used ones that have been extracted from IAPS database.

Peripheral physiological parameters such as the ECG, BVP, GSR, EOG, RSP, and facial EMG (corrugator and zygomatic) will be detected throughout the test as measurable indicators of emotional arousal (T0-T1). Additionally, morning venous blood sampling is planned to analyse biohumoral parameters in subjects with eating disorders, including interleukin 6, cortisol, serotonin, catecholamines, and endorphins at T0 and T1.

PD patients and participants affected by AN will be recruited at the IRCCS Auxologico Piancavallo, at the Neurology and Neurorehabilitation Unit, and the Rehabilitation of eating disorder and Nutrition Unit respectively. Patients will receive all the information required to sign the informed consent form, and inclusion/exclusion criteria will be evaluated by a neurologist and an expert physician in eating disorders.

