In the context of affective flexibility, we will consider transition indicators derived from physiological measuring (ECG, f-EMG, GSR, RSP) and analyzed by the Markov chain models. The choice of Markov chains as our analytical framework stems from their inherent capacity to capture probabilistic transitions between discrete states, a quality that aligns seamlessly with the nuanced shifts and fluctuations observed in affective experiences. By harnessing the capabilities of Markov chains, we dissect the temporal evolution of emotional states and elucidate the underlying patterns that define affective transitions. Our experimental design affords us the opportunity to calculate and evaluate affect variability across different affective transitions, which can subsequently be normalized and integrated into the Markov chains. Initially, we will calculate the reciprocal ratio between the absolute mean and variability of the signal standardized variability measures based on the inverse of Noise to Signal. The standardized variability index is computed for each transition, considering the 30-second interval between blocks (120’’+-15’’) (Fig 5). However, it is also necessary to consider state indexes for each block in the Markov matrix, specifically the transition of state e.g. A to itself, called *state trait transition*. State trait transitions represent the probability of remaining in the same emotional state, and in the Markov Matrix, they are represented as the main diagonal. These state trait indexes are determined during the central 30 seconds of each affective block (from 45 to 75 seconds) Within the Markov matrixes, we will relativize the prior transition variability indexes, to experiment the probability of passing from one affective state to another. Normalization of transition indexes is required because the sum of transitions in Markov matrices is 1.

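### AA, BB, CC and DD are described as the subject's probability of staying in an affective state, but they are computed as relative signal ratios over picture blocks set by the experimenter and cannot carry that meaning

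*Protocol article*

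**What the plan says.** All of this is in the protocol article, Statistical analysis, in the text around Figs 4 and 5, unless noted.

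- **Meaning.** The diagonal is introduced with "State trait transitions represent the probability of remaining in the same emotional state". After Fig 5 the same cells are said to be ones "which convey the subject’s probability of remaining anchored in a specific affective state (stability".
- **What is analysed.** "we extracted and analyzed only the main-diagonal indexes, denoted as state trait indexes (AA-BB-CC-DD". The off-diagonal cells enter only through the normalisation.
- **How a cell is computed.** "Initially, we will calculate the reciprocal ratio between the absolute mean and variability of the signal", described as an inverse noise-to-signal measure. For off-diagonal cells: "The standardized variability index is computed for each transition, considering the 30-second interval between blocks", that is, 15 s on either side of the block change. For diagonal cells: "These state trait indexes are determined during the central 30 seconds of each affective block", from 45 to 75 s.
- **Normalisation.** "Normalization of transition indexes is required because the sum of transitions in Markov matrices is 1".
- **Who sets the sequence.** The Fig 3 legend (Materials and procedure) describes "implementation into a sequence consisting of 13 image blocks, resulting in 12 possible transitions for analysis". The rows and columns of the matrix are the picture quadrants.

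**The concern.** The endpoint has a stated meaning and a stated formula, and they do not agree. A probability of staying needs a state for the subject at each time step and a record of whether the subject stayed or moved. Here the state label comes from the picture on the screen, and the number in the cell comes from the size and variability of a signal in a window. Making positive ratios add to 1 gives proportions of a total; it does not make them estimates of transition probabilities.

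Only these cells carry the affective side of the study, both in the 2x2 ANOVA and in the correlations with the cognitive measures (Fig 4 legend). A change from T0 to T1, or a patient-control difference, would be reported as patients being more or less stuck in an emotional state. The hypothesis that patients gain affective flexibility would be judged on a number whose direction relative to its label depends on which way the ratio is taken.

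**Working it through.** **1. Design figures (Materials and procedure; Figs 3 and 5).** These reproduce:
- 13 blocks x 12 images = 156 images
- 12 images x 10 s = 120 s per block
- 4 quadrants x 3 others = 12 ordered transitions, matching the 12 changes between 13 blocks

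A 13-block path that covers all 12 transitions uses each between-quadrant pair once and each self-pair never. The block sequence therefore holds no information about staying.

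**2. Formula.** Let r_ij be the ratio in the window for cell (i, j). I assume normalisation by row, which is the usual meaning for a Markov matrix but is not spelled out:

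p_ii = r_ii / (sum of the four r_ij in row i)

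**3. Signal that does not respond to the pictures.** Mean and variability are then the same in all windows, so every r is equal:

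p_ii = r / (4r) = 0.25, for any r and for either orientation of the ratio.

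If the whole matrix were scaled to 1 instead, the value would be r / (16r) = 0.0625. A stay probability for such a subject would be 1 for the state occupied and undefined for states never entered, yet the index returns about 0.25 in all four rows.

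To reach a value p, the central-window ratio must be 3p / (1 - p) times each boundary ratio: 3 x 0.90 / 0.10 = 27 times for 0.90, and 3 x 0.99 / 0.01 = 297 times for 0.99.

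**4. Signal that follows the pictures (simulation).** The assumptions are mine, not the plan's: mean 10, noise SD 1, 4 samples per second, four equally spaced quadrant levels, random 13-block paths, central windows averaged over the 3 or 4 blocks of a quadrant, and 200 subjects per setting. Mean of the four diagonal cells:

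| Level step (SD) | mean/SD, independent noise | mean/SD, AR(0.9) noise | SD/mean, independent noise | SD/mean, AR(0.9) noise |
|---|---|---|---|---|
| 0 | 0.250 | 0.250 | 0.251 | 0.251 |
| 0.5 | 0.267 | 0.268 | 0.234 | 0.233 |
| 1 | 0.301 | 0.307 | 0.202 | 0.198 |
| 2 | 0.374 | 0.386 | 0.149 | 0.142 |

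The mechanism is simple. A level change inside the boundary window inflates its SD. Under mean/SD this lowers the off-diagonal ratios and raises the diagonal share; under SD/mean it does the opposite.

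**5. A direct shift measure at the block changes.** I also checked the absolute difference between the 15 s before and the 15 s after each change, divided by the within-block SD and averaged over the 12 changes. A subject with no level change scores about 0.15 with independent noise, but about 0.6, 0.8 and 1.0 with AR(0.9), AR(0.95) and AR(0.98) noise. A genuine 0.5 SD step with independent noise scores about 0.84. Autocorrelation alone therefore lifts the measure well above zero.

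**The case against.** **The index is openly a standardised variability measure.** The section says the indexes are made relative before they enter the matrix, so there is one computation with an over-strong label, not two rival computations. This stands. A reader might infer that the 2x2 ANOVA is invalid. The documents do not support that: the test of whether the index differs by group or time is unaffected, and so are its type I error and the sample size.

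**The inversion is partly a matter of reading.** A reader might infer that a subject who follows every picture change has a true stay probability of 0, so that scores of 0.15 to 0.37 are plainly wrong. That depends on stepping the chain from block to block. Stepped image by image, the same subject stays in 143 of 155 steps (156 images give 155 steps, less 12 switches), or 0.92. The plan fixes no step, so no true value of 0 can be set against the index. A subject who is steady within blocks and shifts between them could also reasonably have a high diagonal. What remains is that such a subject should not be called anchored, in the sense of inflexible.

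**The 0.25 is conditional.** It needs row normalisation and equal mean and variability across windows; drift or habituation would move single cells. A flat response may also come from a channel that does not register affect, so a reader should not infer that every patient who never changes state scores 0.25 where 1 is correct.

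**Not everything is visible.** Fig 5 is not shown and the article condenses a fuller protocol, so it cannot be said that no classification of the subject's state exists anywhere. The text nevertheless gives both the meaning and the formula, and the conflict lies between those two.

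**Conclusion.** The concern holds as a mismatch between what AA, BB, CC and DD are said to measure and how they are computed. They are each quadrant's within-block share of a set of signal ratios, not the subject's probability of staying in a state.

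The firm part is algebra: with row normalisation, a signal that does not respond to the pictures gives 0.25 in every row under either orientation. The values for responsive signals, about 0.27 to 0.37 (mean/SD) or 0.23 to 0.15 (SD/mean) for steps of 0.5 to 2 SD, rest on the simulation assumptions above. They show direction and rough size only. The inverse noise-to-signal description points to mean/SD, under which a stronger response to the pictures raises the score labelled as anchoring. Because the text also calls the result a variability index, the orientation is not settled.

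The data and the planned test remain usable. What is not supported is a conclusion about emotional persistence or anchoring.

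**What to change.** In Statistical analysis, in the Markov chain text before and after Fig 5:

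1. Stop describing AA, BB, CC and DD as a probability of staying or of being anchored. Describe and report them as a relative within-block versus block-boundary signal ratio.
2. State the orientation of the ratio (mean/SD or SD/mean) and that normalisation is by row, if that is what is meant.
3. State that no conclusion about emotional persistence will be drawn from these cells.
4. Optionally add the shift measure at the 12 block changes, as a supportive analysis only. Reference it to each subject's own no-change level, for example the same 15 s versus 15 s difference taken within blocks (45-60 s against 60-75 s fits the existing central window). Without that reference, a change in autocorrelation between T0 and T1 could pass for a change in flexibility. The referenced version was not simulated here and should be tried on pilot or simulated signals first.

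The cost is a change of wording and, if wanted, one derived variable from signals already recorded. The downside is that the results can no longer be presented as Markov transition probabilities.

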### Sample size

The sample size was calculated using Gpower 3.1, separately for PD and AN population class. For eating disorders, the study by Sierra and colleagues [82] was used to estimate effect dimension: in the study, IAPS (International Affective Picture System) results were used as a variable dependent on predictive variables describing the emotionality of patients, such as the PANAS (Positive and Negative Affect Schedule). In order to be more conservative and with an effect size of 0.34 and a statistical power of 0.95, we project about 40 subjects, considering eventually drop-out, for the patient and control groups, respectively.

**F tests—**ANOVA: Repeated measures, within-between interaction

**Analysis:** A priori: Compute required sample size

**Input:** Effect size f   = 0.34

   α err prob   = 0.05

   Power (1-β err prob)   = 0.95

   Number of groups  = 2

   Number of measurements = 2

   Corr among rep measures = 0.5

   Nonsphericity correction ε = 1

**Output:** Noncentrality parameter λ = 14.7968000

   Critical F   = 4.1708768

   Numerator df   = 1.0000000

   Denominator df  = 30.0000000

   Total sample size  = 32

   Actual power   = 0.9608705

The study by Ille and colleagues [83] was used to estimate the effect dimension of PD group: The study used IAPS to investigate patients’ emotional reactions. In order to be more conservative and with an effect size of 0.39 and a statistical power of 0.95, we project about 30 subjects, considering eventually drop-out, for the patient and control groups, respectively.

**F tests—**ANOVA: Repeated measures, within-between interaction

**Analysis:** A priori: Compute required sample size

**Input:** Effect size f   = 0.39

   α err prob   = 0.05

   Power (1-β err prob)  = 0.95

   Number of groups  = 2

   Number of measurements = 2

   Corr among rep measures = 0.5

   Nonsphericity correction ε = 1

**Output:** Noncentrality parameter λ = 14.6016000

   Critical F   = 4.3009495

   Numerator df  = 1.0000000

   Denominator df  = 22.0000000

   Total sample size  = 24

   Actual power  = 0.9544574

Control groups will be paired by age and gender relative to patient groups.

Top of Form

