### Rehabilitation

Between the assessment phases, participants will be allocated to a rehabilitation program. It will be different based on the group: 15 days for PD and 4 weeks for anorexia patients.

PD will participate in a daily rehabilitation program from Monday to Saturday including one hour of physical therapy each day. Patients will be guided by a physiotherapist as they complete exercises that improve gait speed, walking ability, and balance. Depending on the patient’s comorbidities, the additional two hours per day may involve one or more of the following activities: rehabilitation psychology, speech and swallow therapy, language therapy, cognition therapy, and therapies oriented toward daily function and community reintegration.

Instead, patients with AN will go through 4 weeks of rehabilitation based on refeeding in a medical setting. The refeeding program is implemented by a multidisciplinary team of doctors, dietitians, educators, and psychologists. The following criteria form the basis of the refeeding strategy: Higher calorie feeding is preferred in moderately malnourished patients with AN; meal-only approaches or combined nasogastric plus meal-feeding approaches are taken into consideration based on patient compliance; higher calorie refeeding strategies appear safe in severely malnourished patients with AN in the presence of medical monitoring and electrolyte correction.

As a crucial step in assisting the refeeding process, the rehabilitation psychology program will be coordinated and supervised by the psychologist with the aid of the educator, with daily individual meetings.

Patients who can support physical activity will go through a standardized rehabilitation program: during these 4 weeks, they will be directed by a physiotherapist through exercises to improve their walking ability and endurance, and balance control an hour a day, from Monday through Saturday. The proposed rehabilitation is an element of clinical routine, and we need to understand whether and how mental flexibility, encoded in its cognitive-affective dimensions, is a trait or state dimension. Patients, after routine rehabilitation performed in the hospital, might have an improvement in the affective-cognitive components of MF [53].

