### Statistical analysis

The statistical methodology employed in this study centers around a 2x2 univariate analysis of variance (ANOVA) model. In this model, the between-subjects factor encompasses the distinction between patients and controls, while the within-subjects factor is delineated by the acute phase upon hospitalization (T0) and post-rehabilitation (T1). The primary objective of adopting a univariate approach is to systematically assess the effects of both group membership and time on measures of cognitive flexibility and affective flexibility. Furthermore, we seek to investigate potential interaction effects that may exist between these factors (Fig 4).

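### Stability of flexibility in controls is inferred from a non-significant T0–T1 difference, which the planned control groups are too small to support; the group-by-time interaction is unaffected

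*Protocol article*

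**What the plan says.** The hypotheses that close the Statistical analysis section (after Fig 5) begin with the controls: "we hypothesize that there will be no statistically significant differences between the scores obtained at T0 and T1", for both cognitive and affective flexibility. The next sentence interprets this: "This expectation suggests that individuals in the control group are likely to maintain stable levels of cognitive and affective flexibility over time". The second hypothesis expects a group-by-time interaction, with patients improving. The section then presents the two hypotheses as the framework for the analysis.

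The model is a 2×2 ANOVA, patients versus controls by T0 versus T1, run for each flexibility measure (Statistical analysis; Fig 4 legend). Both calculations in the Sample size section are for one test: "ANOVA: Repeated measures, within-between interaction". Neither concerns the change within controls.

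The Rehabilitation section adds a wider question: "we need to understand whether and how mental flexibility, encoded in its cognitive-affective dimensions, is a trait or state dimension". It is raised about patients who go through routine rehabilitation.

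**The concern.** A test that fails to reject no change does not show that there was no change. When non-significance is the predicted result, a smaller or noisier control group makes the prediction easier to meet. Some drift is plausible on the article's own description: the Assessment section repeats the same tests at T1, 15 days or 4 weeks after T0, and several of them are timed or rule-discovery tasks on which a second attempt may go better.

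What is at stake is the statement that flexibility scores stay stable in people who are not patients. The project aims to give clinicians an assessment framework, so a reader could take that statement as evidence that the scores hold steady on retest.

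**Working it through.** **1. The plan's own figures reproduce.** For the within-between interaction with m = 2 measurements and correlation ρ = 0.5, λ = f²·N·m/(1−ρ), with 1 and N−2 degrees of freedom.

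- AN: 0.34² × 32 × 2/0.5 = 14.7968; critical F 4.1709; power 0.9609. Agrees with the Sample size section.
- PD: 0.39² × 24 × 2/0.5 = 14.6016; critical F 4.3009; power 0.9545. Agrees.

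At ρ = 0.5 these effect sizes correspond to a difference in change between groups of 4f, which is 1.36 SD (AN) and 1.56 SD (PD). The calculation says nothing about detecting a modest change within controls.

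**2. Inputs for the control comparison.**

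- Two-sided α = 0.05 and ρ = 0.5, from the Sample size section.
- SD of change = SD × √(2(1−ρ)) = SD × √1 = SD. At ρ = 0.5, SD of change and SD of the score are therefore the same unit.
- Number of controls: the section projects about 40 (AN) and about 30 (PD) for the patient and control groups. Read per group, this gives 40 and 30 controls. Read as totals, it gives 20 and 15.
- True drift in controls: not in the document. Values of 0.2, 0.3 and 0.5 SD are assumed to show the range.

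**3. Chance that a real drift is non-significant.** Paired t test with n−1 degrees of freedom and noncentrality d√n. For example, n = 40 and d = 0.3 gives 0.3 × √40 = 1.897 against a critical t of 2.023. The 95% half-width is t/√n, taking the observed SD of change to be 1.

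| Controls | Critical t | Drift 0.2 SD | Drift 0.3 SD | Drift 0.5 SD | 95% CI half-width |
|---|---|---|---|---|---|
| 40 | 2.023 | 0.765 | 0.543 | 0.131 | 0.32 SD |
| 30 | 2.045 | 0.815 | 0.645 | 0.246 | 0.37 SD |
| 20 | 2.093 | 0.864 | 0.753 | 0.435 | 0.47 SD |
| 15 | 2.145 | 0.888 | 0.808 | 0.562 | 0.55 SD |

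Sensitivity: with ρ = 0.7 (also an assumption) and 40 controls, a drift of 0.2, 0.3 or 0.5 SD of the score is missed in 64%, 33% and 2% of studies.

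**4. What an equivalence claim could deliver.** Two one-sided tests at 5% each (90% interval inside ±margin), true change zero, ρ = 0.5. The margins are assumptions.

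| Controls | Power, margin ±0.3 SD | Power, margin ±0.5 SD |
|---|---|---|
| 40 | 18% | 86% |
| 30 | 6% | 70% |
| 20 | 1% | 39% |
| 15 | <1% | 20% |

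For 80% power, a ±0.5 SD margin needs 36 controls and a ±0.3 SD margin needs 96. The wider margin is within reach only under the per-group reading for AN, and it would count a true 0.3 SD drift as acceptable.

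**The case against.** The strongest reply is that the test that matters is the interaction. It is the test the study was sized for, it compares the two groups' changes directly, and a practice gain of equal size in both groups cancels. It does not require controls to be stable. This stands, and it limits the point to the statement about controls.

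A reader might infer that the trait-versus-state question will therefore be answered wrongly. The article does not support this. The Rehabilitation section raises that question about patients and follows it with the possibility that they improve. Nowhere is it to be decided by the control comparison.

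It can also be said that the article describes anticipated outcomes in cautious words and sets no formal decision rule. That is fair as to tone. Still, the expected result is defined by significance, and stability is the only reading offered for it.

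The size of the problem depends on an assumed drift. With 40 or 30 controls a 0.5 SD drift would usually be detected, being missed 13% and 25% of the time, so the weakness concerns small to moderate drift unless the projected numbers are totals.

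Finally, a test-retest coefficient and the exact retest interval for controls are details that a condensed article may leave to the full protocol. Their absence is not held against the plan.

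**Conclusion.** The point holds for the control-stability statement only. With the planned numbers, a true drift of 0.3 SD of change would be non-significant in about 54% (40 controls) to 65% (30 controls) of studies, or 75–81% with 20 or 15 controls. For a 0.5 SD drift the figures are 13–25% and 44–56%. A non-significant result is therefore common with and without real drift, and cannot support stability.

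These figures rest on the article's α and ρ = 0.5, on assumed drift sizes, and on the two readings of the projected numbers. A higher correlation lowers them for a drift of given size on the score scale.

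The interaction test remains valid as a test of differential change. Only patients undergo the admission, and they are first assessed in its acute phase. An interaction therefore shows change over an admission relative to controls and does not isolate the contribution of rehabilitation.

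**What to change.** 1. Replace the non-significance hypothesis with estimation: for each flexibility score, report the mean T1−T0 change in controls with its confidence interval.
2. Claim stability only if that interval (90% for two one-sided tests at 5%) lies wholly inside a margin fixed before the data are seen and justified for the score. A ±0.5 SD margin would accept a 0.3 SD drift, so choosing it means stating that such a drift does not matter.
3. Rest the main conclusion on the group-by-time interaction, and word it as change over a routine admission relative to controls.

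No extra participants or assessments are needed; the change is to the hypotheses and the reporting of data already planned. The downside is that, with these group sizes, many measures may have to be reported as stability not shown, especially under a narrow margin or if there are only 15 to 20 controls.
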